## Abstract

The proposed research aims to test the effects of a two-month yoga-breath linked intervention to stop smoking (Y-BLISS) as an add-on to standard treatment in tobacco use disorder (TUD; in the form of cigarette smoking) by conducting a randomized controlled study with the following primary outcome variable: number of cigarettes smoked per day. Secondary outcome variables are motivation to stop smoking, craving, dependence severity, lung capacity, and exhaled carbon-monoxide, and 7-day point-prevalence abstinence (7PPA). In this single-blinded, randomized, controlled, parallel-group superiority trial with 1:1 allocation ratio, 100 patients with TUD availing the outpatient/inpatient clinical services at a tertiary mental healthcare hospital in India will be enrolled after giving informed consent. Consecutive consenting patients will be randomly allotted to one of the two groups – yoga arm (Y-bliss arm), or desktop exercise arm (D-exercise arm). Allocation concealment will be followed, the clinicians, outcome assessors and data analysts will remain blind to subject-group allocation. A validated and standardized 12-minute yoga program (Y-BLISS) for TUD will be used as an intervention. The control group will receive an equivalent 12-minute desktop exercise module. Participants in respective arms will receive 40 online supervised sessions over 8 weeks, 5 sessions per week in the mornings as they will be asked to practice the same on an as-neededs basis whenever they feel cravings for cigarette smoking. Assessments will be done at baseline, 4th week and 8
^th^ week. Data from all randomized subjects will be analyzed using intent-to-treat analysis and mixed model multivariate analysis. Dissemination Findings will be disseminated through peer-reviewed publications, conference presentations, and social media. Trial registration number The trial has been registered under Clinical Trials Registry India (CTRI) with the registration number: CTRI/2022/12/048117, date of registration: 14
^th^ December 2022.

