### Sample size estimation

Sample size is estimated using G*Power software based on parameters derived from a study with similar design (
Jeffries *et al.*, 2020) effect size d = 0.59, α = 0.05, two-tailed, power (1 − β) = 0.95. The calculation yielded a requirement of n = 100 analyzable participants (50 per group). To account for an anticipated post-randomization attrition rate of 30%, the recruitment target was inflated using the standard formula N_randomized = N_completers ÷ (1 − attrition rate), giving 100 ÷ 0.70 ≈ 143 participants to be randomized. A final sample of 144 participants will therefore be recruited, with 72 participants in each arm.

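### The abstract says 100 patients will be enrolled, but the sample-size section makes 100 the analysable number and 144 the number recruited

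*Protocol article*

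**What the plan says.** The abstract describes a 1:1 randomised trial in which "100 patients with TUD availing the outpatient/inpatient clinical services at a tertiary mental healthcare hospital in India will be enrolled after giving informed consent". Its next sentence has consenting patients randomised to the yoga or the desktop-exercise arm, so 100 is a count taken at consent, before allocation.

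The Sample size estimation section starts from "effect size d = 0.59", "α = 0.05, two-tailed" and "power (1 − β) = 0.95". It reports the result as follows: "The calculation yielded a requirement of n = 100 analyzable participants (50 per group"). It then allows for 30% attrition after randomisation, divides 100 by 0.70 to reach about 143, and concludes: "A final sample of 144 participants will therefore be recruited, with 72 participants in each arm".

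The Data analysis section plans an intention-to-treat mixed-model analysis of everyone randomised. No section explains why the abstract and the sample-size section give different recruitment figures.

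**The concern.** One number has two meanings. In the abstract, 100 is how many patients enter the trial. In the sample-size section, 100 is how many must still be analysable once 30% have been lost. The two recruitment targets differ by 144 − 100 = 44 participants.

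The target sample size decides when recruitment ends, and the abstract is the part of the article most often read and copied elsewhere. Anyone who takes the target from it gets a figure with no allowance for the attrition that the protocol itself expects. The power that goes with that figure is lower than for the sample-size section's target.

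**Working it through.** **Inputs.** From Sample size estimation: d = 0.59, two-sided alpha 0.05, stated power 0.95, 100 analysable (50 per group), attrition 30%, 144 recruited (72 per arm). From the abstract: 100 enrolled. From Trial design: 1:1 allocation.

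**Step 1: the inflation for attrition.** Number randomised = analysable ÷ (1 − attrition) = 100 ÷ 0.70 = 142.9, so 143, and 144 for equal arms. This reproduces. Going back, 144 × 0.70 = 100.8, or about 50 analysable per arm. The sample-size section is consistent in how it moves from 100 to 144.

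**Step 2: the abstract's figure under the same attrition.** 100 × 0.70 = 70 analysable, or 35 per arm.

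**Step 3: power on the basis of analysable participants.** For a two-sample t test with n per arm, the noncentrality is d × √(n/2) on 2n − 2 degrees of freedom. In the normal approximation, power is Φ(d × √(n/2) − 1.96).

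| Enrolled | Analysable per arm | Noncentrality | Power, noncentral t | Power, normal |
|---|---|---|---|---|
| 100 | 35 | 0.59 × √17.5 = 2.47 | 68.2% | 69.4% |
| 144 | 50 | 0.59 × √25 = 2.95 | 83.2% | 83.9% |

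The difference between the two recruitment figures is 83.2 − 68.2 = 15.0 percentage points.

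**Step 4: the stated 95%.** This does not reproduce from 50 per arm.

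- Normal approximation: n per arm = 2 × (1.960 + 1.645)² ÷ 0.59² = 25.99 ÷ 0.348 = 74.7, so 75 per arm (150 in total).
- Noncentral t: 76 per arm (152 in total), with power 95.1%.
- At 30% attrition, 152 ÷ 0.70 = 217.1, so 218 randomised.
- A total of 100 does arise for the same d with a one-sided 0.05 test and 90% power (50 per arm, 90.1%), but those are not the stated inputs.

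The distance from the stated 95% to the 68% therefore has two parts. About 12 points (95 to 83.2) come from the sample-size calculation itself. The other 15 points (83.2 to 68.2) would come from enrolling the abstract's number.

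**The case against.** The strongest reply is that the operative section is not ambiguous. Sample size estimation labels 100 as analysable, shows the division by 0.70 and arrives at 144. Nobody working from it would take 100 as the recruitment target, and nothing in the article says that the team means to stop there. This stands. It makes the 68% the consequence of following the abstract, not a forecast of what the trial will do. The abstract still states a different enrolment total, and a condensed text may omit detail but should not give another number.

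The abstract's 100 might also be read as clinic patients only, since the Study setting section adds screening at a well-being centre and through social media. No section divides the target by source, however, and the abstract presents 100 as the trial's enrolment.

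The power figures treat participants lost to follow-up as contributing nothing. The planned mixed model on all randomised participants may recover some information from those with week-4 data, so actual power could differ. This stands as a caveat. The protocol sizes the trial on analysable participants, so the comparison is made on its own basis, and the inconsistency does not depend on it.

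Three stronger readings are tempting but not supported:

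- A reader might infer that the abstract's error costs the whole fall from 95% to 68%. It accounts only for the step from 83% to 68%.
- A reader might infer that reaching 144 would look like a data-driven change. Both numbers stand in the same document, and the reason given for 144 is an attrition assumption that uses no trial data. The Data analysis section does allow sample-size adjustment after interim results, but nothing links 144 to that provision.
- A reader might infer that the registry or consent documents are wrong. They are not shown, so this cannot be judged.

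**Conclusion.** The inconsistency is real and should be corrected. The abstract gives as the enrolment total a number that the sample-size section defines as what remains after attrition. The division by 0.70 is correct, so this is a conflict between abstract and body and not a slip in the inflation step.

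On the protocol's inputs (d = 0.59, two-sided 0.05, 30% attrition, equal arms, a t test on analysable participants), enrolling 100 would give about 68% power and enrolling 144 about 83%. Neither figure delivers the stated 95%. That shortfall is a separate error in the sample-size section, and aligning the abstract to 144 does not remove it.

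**What to change.** In the abstract, replace the figure of 100 enrolled with 144 participants randomised, 72 per arm, to give about 100 analysable. The word analysable is safer than completer here, because the Adherence monitoring section gives completer its own definition (at least 20 of 40 sessions plus the week-8 assessment).

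In the same revision, restate in Sample size estimation that 50 analysable per arm gives about 83% power at d = 0.59, two-sided 0.05. If the sponsor instead wishes to keep 95%, the target itself changes to about 152 analysable and about 218 randomised, and that number must then appear in both places. Settling this first avoids correcting the abstract twice.

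Confirm that the trial registry and the consent documents carry the same number.

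With 144 kept, the cost is a line in the abstract, a line in the sample-size section and a check of those two records. Design and conduct do not change.

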## Background

Tobacco smoking is a worldwide epidemic with more than one billion consumers. Tobacco consumption is one of the commonest addictions and is a leading cause of morbidity and mortality worldwide. The World Health Organization estimates 8 million casualties every year resulting from tobacco consumption (
Reitsma *et al.*, 2021). The most prevalent, and widely researched form of tobacco consumption is cigarette smoking. In India, 19 percent of the male, and 2 percent the female adult population smoked tobacco as per survey done in the year 2016–2017 (
GATS, 2016). More recent National Family Health Survey (
NFHS 5, 2021) found an overall prevalence of tobacco use to be 40.3% (39% in men; 4% in women) with 13.3% of them smoking cigarettes. Cigarette smoking is reported to be the cause of premature death in every one out of two dependent users. About half of all tobacco-related deaths occur between the ages of 35 and 69, resulting in a loss of 20 to 25 years of life expectancy compared to non-smokers (
Jha *et al.*, 2006). These adverse effects have been found in both male and female populations. Research has shown that females are more susceptible to smoking-related morbidity and mortality (
Allen *et al.*, 2014).

The Government of India enacted the ‘Cigarettes and Other Tobacco Products (Prohibition of Advertisement and Regulation of Trade and Commerce, Production, Supply and Distribution) Act (COTPA) in 2003, and revised in 2008. The aim of the Act was to prohibit the consumption of cigarettes and other tobacco products, which are injurious to health. The revision in 2008 focused on redefining ‘public places’ to include all workplaces and authorising personnel responsible for enforcement of the law for maintaining smoke - free public places across the country (
Gupta *et al.*, 2024).

Conventionally, both pharmacological and non-pharmacological approaches are helpful in improving smoking abstinence. Mainstay of pharmacotherapy is nicotine replacement therapy (NRT) in the form of nicotine patch, gum, lozenge, nasal spray and oral inhaler. Non-nicotine medications such as Bupropion, Varenicline tartrate are the other useful options. Non-pharmacological interventions with proven utility in smoking cessation include behavioural therapies such as counselling, support groups, telephone quit-line, physical exercises, and mindfulness approaches (
Jha & Li, 2017). Pharmacological therapies though effective in reducing craving, are costly and the non-pharmacological approaches are not easily accessible especially in country like India where there is a large gap between the demand and supply of trained human resource in psychotherapy. Moreover, a need for culturally sensitive interventions has been emphasized. Smoking cessation can be very challenging. A study showed that at any given point of time 70% of smokers had the desire to quit and 46% had attempted to quit but were not able to maintain abstinence. Over 50% of these subjects had relapsed in the past one year (
Koçak *et al.*, 2015). Psychosocial stressors increase the chances of relapse following a quit attempt (
Shiffman *et al.*, 1996). Study showed that smokers who failed to quit or relapsed after a short period reported high levels of stress prior to quitting after cessation. On the other hand, participants who were able to quit and maintain abstinence at 6-month follow-up reported a gradual decrease in stress levels (
Cohen & Lichtenstein, 1990).

Considering the above, there is a need for a low cost, scalable, culturally more acceptable intervention that can generate a feeling of self-empowerment in the practitioner. One such initiative in India is the use of digital technology, exemplified by the NIMHANS Tobacco Quitline Services (NTQLS) implemented by the National Institute of Mental Health and Neurosciences, Bangalore (
Pradeepkumar *et al.*, 2023). Another promising approach could involve leveraging traditional therapies, such as yoga. Yoga and meditation are increasingly recognized for their ability to enhance recovery from addiction by targeting stress-related cognitions, emotions, and behavioral urges such as craving. The insights and self-awareness learned through yoga practice (which differentiate it from exercise can target multiple psychological, physiological, and behavioral processes that are implicated in addiction and relapse (
Khanna & Greeson, 2013). While exploring novel interventions is important, efforts should also focus on increasing the number of tobacco cessation centers in India (
Narasimha *et al.*, 2021). These centers can play a crucial role in delivering such interventions effectively at the community level.

In light of the above, a systematic research plan to understand role of yoga-breath linked intervention to stop smoking (Y-BLISS) as an adjuvant in the management of cigarette smoking dependence is proposed.

## Objectives

### Primary objectives

To evaluate the effect of a two-month add-on Y-BLISS program on number of cigarettes smoked per day in participants with nicotine dependence in the form of smoking cigarettes.

### Secondary objectives

To evaluate the effect of a two-month add-on Y-BLISS program as compared to an equivalent desktop exercise program (D-exercise) on
1.motivation to stop smoking using Motivation to Stop (MTSS) Scale2.craving of smoking using tobacco craving questionnaire3.dependence severity using FTND4.exhaled carbon monoxide [Exhaled CO] using Bedfont Breath Analyzer5.lung capacity using peak flow meter (liters/minute)6.7-day point-prevalence abstinence (7PPA) using self-report with biochemical verification by exhaled carbon monoxide (≤10 ppm indicating abstinence).

### Hypothesis

The Y-BLISS program will serve as a useful adjunct therapy to standard treatment as compared to D-exercise program in participants with cigarette smoking dependence in.

Primary-1) reducing number of cigarettes smoked per day.

Secondary-1) improving motivation to stop smoking, 2) reducing craving, 3) reducing dependence, 4) improving lung capacity and 5) reducing exhaled carbon mono-oxide, and 6) increasing 7-day point-prevalence abstinence.

## Plan for research

### Trial design

Single-blinded, randomized, controlled, parallel group superiority trial with a 1:1 allocation ratio.

### Sample size estimation

Sample size is estimated using G*Power software based on parameters derived from a study with similar design (
Jeffries *et al.*, 2020) effect size d = 0.59, α = 0.05, two-tailed, power (1 − β) = 0.95. The calculation yielded a requirement of n = 100 analyzable participants (50 per group). To account for an anticipated post-randomization attrition rate of 30%, the recruitment target was inflated using the standard formula N_randomized = N_completers ÷ (1 − attrition rate), giving 100 ÷ 0.70 ≈ 143 participants to be randomized. A final sample of 144 participants will therefore be recruited, with 72 participants in each arm.

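### The sample size does not follow from its stated inputs: with d = 0.59, two-tailed alpha 0.05 and 50 analysable per group, power is about 83%, not 95%

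*Protocol article*

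**What the plan says.** Under Sample size estimation, the protocol article says G*Power was used with "effect size d = 0.59, α = 0.05, two-tailed, power (1 − β) = 0.95", the parameters being taken from an earlier study of similar design. It then states: "The calculation yielded a requirement of n = 100 analyzable participants (50 per group". Next it allows for an "anticipated post-randomization attrition rate of 30" per cent, divides 100 by 0.70 to reach about 143, and concludes: "A final sample of 144 participants will therefore be recruited, with 72 participants in each arm".

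The Trial design section describes a "parallel group superiority trial with a 1:1 allocation ratio". The sample size text names no test family, number of repeated measurements, correlation between measurements or covariate adjustment.

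**The concern.** The section prints both the inputs and the output of a standard calculation, so a reader can check one against the other. For two equal groups, a standardised difference of 0.59 at 95% two-sided power should need roughly 75 per group, and 50 is about a third too low.

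This is the trial's only stated justification for its size. If the power is overstated, a null result on cigarettes per day would be read as coming from a trial with a 5% chance of missing the assumed effect, when the stated inputs imply more than three times that. The Data analysis section also lets the sample size be adjusted after an interim analysis, and any such decision would start from the wrong power.

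**Working it through.** **Inputs** (protocol article, Sample size estimation and Trial design): d = 0.59; alpha = 0.05, two-tailed; power 0.95; 1:1 allocation; 50 analysable per group; attrition 30%; 144 randomised (72 per arm). The test is not named. A two-sample t test is inferred from the use of d, two tails and a per-group n in a two-arm design.

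**1. Try to reproduce 50 per group.** Normal approximation:

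n per group = 2(z₀.₉₇₅ + z₀.₉₅)² / d² = 2(1.960 + 1.645)² / 0.59² = 2 × 12.996 / 0.3481 ≈ 74.7, so 75 per group (150 in total).

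The exact noncentral t calculation gives 75.6, so 76 per group (152 in total); power is 94.8% at 75 and 95.1% at 76. The stated 100 is not reproduced by either method.

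**2. Power at the stated size.** The noncentrality is d√(n/2) = 0.59 × √25 = 2.95. The normal approximation gives Φ(2.95 − 1.96) = Φ(0.99) ≈ 83.9%. The exact t value is 83.2%, so the type II error is 1 − 0.832 = 0.168, against 0.05 declared (a ratio of 3.4).

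| Analysable per group | Power, d = 0.59, two-sided 0.05 (exact t) |
|---|---|
| 50 | 83.2% |
| 50.4 (144 × 0.70 / 2) | 83.5% |
| 72 (no loss) | 94.0% |
| 76 | 95.1% |

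**3. Effect detectable with 95% power at 50 per group:** d = 0.73.

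**4. Attrition step.** 100 / 0.70 = 142.9, so 143, rounded to 144: correct as arithmetic. From the recomputed base, 152 / 0.70 = 217.1, so 218 randomised.

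**5. Do other settings give 50 per group?**

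| Setting | Result |
|---|---|
| One-sided 0.05, 95% power | 62.9, so 63 per group |
| One-sided 0.05, 90% power | 49.9, so 50 per group, but contradicts the stated tails and power |
| Two-sided, 80% / 85% / 90% power | 46.1 / 52.6 / 61.3 per group |
| Paired t test, 95% power | 39.3, so 40 in total |
| ANCOVA, baseline correlation 0.57 / 0.60 (normal approximation) | 51 / 48 per group |
| Repeated-measures between-factors, f = d/2 = 0.295, 3 measurements, correlation 0.5 | 102 in total; 94.7% power at 100 |
| Same, 2 measurements, correlation 0.3 | 100 in total |
| Same, 3 measurements, correlation 0.7 | 122 in total; 90.4% power at 100 |

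The correlations in the last four rows are assumptions made for this check. None is in the protocol.

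**The case against.** The strongest reply is that the section never says a two-sample t test was used. Cigarettes per day is measured at baseline, week 4 and week 8, and the Data analysis section plans a mixed model. A calculation that uses the baseline or the repeated measures can come close to 100 at 95% power, as the table shows. This stands to one extent: the 83% is conditional on the t-test reading, and the sponsor may have run something else. It does not rescue the text, because each alternative needs an input that the section does not give, and the match is sensitive to it. With three measurements, moving the correlation from 0.5 to 0.7 takes power at 100 from 94.7% to 90.4%. A between-factors calculation with three measurements would also average in the baseline, where no treatment effect exists.

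A second reply is that all 144 enter the intent-to-treat analysis, which gives about 94%. That needs complete outcome data. A mixed model may recover something from participants with only a week 4 value, but the section itself expects 30% loss and attaches its power to the 100 analysable participants.

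The match with a one-sided test at 90% power is only a possible origin. Other settings also land near 50, so nothing should be built on it. It is fair to add that 83% exceeds the common 80% benchmark and that the type I error is unaffected: the fault is in the stated power, not in the validity of the comparison.

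**Conclusion.** The concern holds. On the printed inputs, 100 analysable participants give 83.2% power rather than 95%, a shortfall of about 12 percentage points. Equivalently, 95% power would need 152 analysable, 52 more than stated. Rounding, or the choice of normal or t distribution, moves these figures by less than one point of power and two participants, so it cannot explain the gap. The 143/144 inflation is computed correctly on a base that the inputs do not support.

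The conclusion rests on reading the calculation as a two-sample t test. If a different test was used, the section is still wrong as written, because the inputs it lists are then incomplete.

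**What to change.** Check the G*Power output, keep 144 randomised, and make the text match in one of two ways.

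- *If a two-sample t test was used:* delete the 0.95 claim and write, for example: With 100 analysable participants (50 per arm), a standardised difference of 0.59 and two-sided alpha 0.05, a two-sample t test has about 83% power; power is about 94% if all 144 randomised participants provide outcome data.
- *If another test was used:* name it and print every input, including the number of measurements, the assumed correlation or covariate, and the source of each, so that 100 can be reproduced.

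In the same edit, reconcile the Abstract, which gives 100 patients as the number to be enrolled, with the 144 in this section.

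The cost is wording only: no extra participants and no change to design or alpha, though under the first option the stated power becomes less favourable. Holding 95% power at d = 0.59 under the t test would instead mean about 218 randomised, but that is not needed to correct the text.

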### Study setting

Participants with at least mild severity of tobacco use disorder (dependence on cigarette smoking with FTND scores above 3) availing the outpatient/inpatient clinical services under the Centre for Addiction Medicine, Department of Psychiatry, and Department of Integrative Medicine, National Institute of Mental Health and Neurosciences (NIMHANS), Bengaluru, India will be approached. Participants will also be screened in the NIMHANS Centre for Well-being and online social media platforms (through an advertisement of the research project). The course of the trial, its benefits, possible demerits, voluntary participation with a choice to quit the study at any time will be explained in simple comprehensible language. Patients satisfying the inclusion criteria will be requested to provide written informed consent. Consecutive consenting patients will be randomly assigned to one of the two groups – Standard treatment + Yoga-breath linked intervention to stop smoking (Y-BLISS arm), or Standard treatment + Desktop Exercises (D-exercise arm) alone by the biostatistician. Allocation sequence will be generated by biostatistician using computer-generated random numbers and allocation concealment will be done using opaque sealed envelopes. A validated and standardized Y-BLISS program will be used as an intervention. Although double blinding will not be possible in the study, the clinicians treating the subjects, the outcome assessors, and data analysts will remain blind to the subject-group allocation status throughout the period of the study. All participants will be continuing their routine standard care (Nicotine replacement therapy and psycho-social support) till the study concludes.
Figure 1 provides the study design outline. Nicotine replacement therapy type and dose will be recorded at baseline, and dosage will be adjusted based on the clinical presentation of the patient by the treating psychiatrist. Any change in nicotine replacement therapy dose, or in concurrent psychotropic or psychotherapeutic treatment, during the trial period will be recorded and logged as a protocol deviation. Baseline nicotine replacement therapy status will be compared between arms and reported together with the baseline characteristics, so that any imbalance is visible to the reader. Cumulative nicotine replacement therapy exposure will not be quantified prospectively and within-trial dose changes will not be modelled as time-varying covariates; this boundary of the design is acknowledged under Limitations.

